## Abstract

**Background:**

Frequent users of emergency medical services for issues that could be more appropriately managed through non-urgent care deplete the limited resources of the health-care system. Community paramedicine is an emerging field that extends the role of paramedics beyond the traditional emergency response. The goal of the current study is to evaluate the impact of a community paramedicine home-visit intervention with frequent users on reducing ambulance calls, hospital visits, and admissions. The study will also provide a cross-sectional description of the characteristics of frequent users of emergency medical services.

**Methods/design:**

An open-label, pragmatic, randomized controlled trial with parallel intervention and control groups will be conducted in four paramedic services in Ontario. The sample size has been calculated as 261 per group for a 25% reduction in ambulance calls. Eligible participants will be frequent callers (three or more calls in 6 months), individuals who call for at least one lift assist, or individuals referred to the program by a paramedic. Individuals will be randomly allocated to receive either the Community Paramedicine at Home (CP@home) program intervention or their usual care (control). Intervention participants will receive up to three visits from a community paramedic, who will conduct health risk assessments, provide health promotion and education, provide referrals to local resources, and fax reports back to the family physician. Data will be collected from administrative databases (e.g., paramedic services), a custom CP@home program database, participant surveys, and key informant interviews. An intention-to-treat analysis will be conducted, including descriptive statistics and multi-level modeling to find factors predictive of primary and secondary outcomes. A thematic analysis will be used to analyze the qualitative outcomes. An economic analysis will consider the cost-effectiveness of the program.

**Discussion:**

CP@home has the potential to reduce the health-care system burden significantly by targeting current frequent users of emergency medical services. By targeting this population, CP@home aims to decrease ambulance calls and emergency department visits, reducing health-care costs and improving the quality of life of a vulnerable population. If successful, CP@home will inform the development of community paramedicine policies and the expanding role of paramedics in regions across Canada.

**Trial Registration:**

ClinicalTrials.gov, NCT02835989. Registered on July 14 2016.

**Electronic supplementary material:**

The online version of this article (10.1186/s13063-018-3107-4) contains supplementary material, which is available to authorized users.

## Background

Frequent 911 calls for emergency medical services (EMS) deplete limited health-care resources. A common, preventable EMS call is when an older adult needs a lift assist; that is, when the individual falls and is unable to pick themselves up due to limited mobility. Some older adults call EMS frequently for lift assists [1–3]. Other preventable calls are from individuals of all ages who repeatedly call EMS for problems that could be handled by more appropriate community and primary care resources, such as for chronic disease management [3]. The average overall cost of the ambulance call and resultant emergency department (ED) visit in Ontario is CAD 1626 [4]. Concurrently, health-care expenditures continue to grow. Therefore, simple interventions that manage common EMS issues related to mobility or pain and reduce risks related to poor mental health, chronic disease, and falls may reduce health-care system burden and provide potential savings.

Community paramedicine (CP) is a promising new extension to paramedicine in which paramedics apply their skills beyond emergency (911) calls to initiate preventative and rehabilitative health and social programs as part of an integrated health-care effort [4–6]. The broad goals of the Community Paramedicine at Home (CP@home) intervention are to decrease complications due to falls, chronic disease, and poor mental health and to improve mobility, quality of life, and health outcomes in vulnerable populations. In doing so, related and more specific goals are also to decrease calls to EMS and ED visits. It is expected that these changes will ultimately lead to more efficient use of health-care resources, improve access to health care, and improve health outcomes among frequent users of EMS.

### Frequent EMS users

Frequent EMS users can be defined as having made four or more calls within 1 year [7–9], though definitions range from three to ten times per year [9–13]. This population falls primarily into two categories: (1) older adults and (2) individuals of all ages with complex health-care needs.

Studies have shown that older adults, those 65 years and older, account for more than a third of all EMS calls related to cardiopulmonary conditions, diabetes, and falls [14–17]. The data indicate that the most frequent users of EMS, hospital transports, and hospital admissions were residents over 65 years old [18]. Recent reports from the Institute for Clinical Evaluative Sciences identified that the level of health-care services used by older adults is driven mainly by the number of chronic conditions they have [19, 20]. Older adults with high comorbidity (>3 chronic conditions) report poorer health, take more prescription medications, and have the highest rate of health-care visits [21]. Consequently, the Institute for Clinical Evaluative Sciences recommends that health-care providers need to work actively with older adults to prevent new chronic conditions and manage existing conditions to avoid complications [19]. In addition, the risk of falls in this population is substantial. It is estimated that one in three persons over the age of 65 is likely to fall at least once each year [22, 23]. Studies in the United States and the United Kingdom suggest that approximately 50% of individuals who call 911 for a lift assist (i.e., have had a fall) will call 911 again within 1 month [1, 2]. Therefore, reducing the risk of falls could have a substantial impact on the health-care system.

Research also indicates that older adults without family support networks have a higher utilization of hospital ED services [24]. An increasing number of older adults are at risk of being socially isolated [25]. This can be due to living alone, the death of family members or friends, retirement, and often, declining health. The World Health Organization reports that social isolation is related to “increased rates of premature death, lower general well-being, more depression, and a higher level of disability from chronic diseases” [26]. With a growing population of individuals over the age of 65 in Canada [27], it is expected that this demand for ED services will increase.

The second category of frequent users of EMS are those with complex needs, who are often further categorized into sub-groups defined by chronic illnesses and mental health issues, including substance abuse [9]. These are preventable and often non-emergent issues that could be handled by primary care. A systematic review by Scott and colleagues in 2014 [9] found no studies on the characteristics of frequent EMS users in Canada, a gap in the available literature. However, a 2015 study in the United Kingdom, which has a universal health-care system like that in Canada, found that frequent callers are a heterogenous group with complex needs [3]. Of the frequent callers, 55% were females and the mean age was 57.6 years, but with a large range (15–98 years) and standard deviation (21.4 years). The most common caller characteristics were frequent medical or clinical needs (64%), mental illness (40%), elderly (38%), unmet social or personal care needs (25%), substance abuse (24%), frequent faller (23%), and high anxiety (11%). The majority of callers had two or more of these characteristics. In this population, 83% required more than one intervention by a case manager and 30% required three or more interventions [3]. In this study, through appropriate interventions, they were able to reduce the median number of EMS calls per individual from five per month to zero per month [3]. This suggests that by implementing interventions linking frequent callers with appropriate preventative and rehabilitative resources in primary care, there may be a beneficial impact on health and health resource utilization.

### An innovative and novel approach to facilitating appropriate health-care use

In 2012, a report by the leadership of Ontario’s Seniors Strategy highlighted the need to deliver innovative, community-based care with the dual goals of enabling older adults to live safely in their own homes and alleviating related pressures on more costly care settings such as acute care hospitals and long-term care services [28]. Current approaches being explored by governments include looking for programs that reallocate existing resources to decrease the unnecessary use of ED resources. The 2012 report recommended a team-based approach, including exploring the expansion of CP programs to support primary care access for older adults [28]. A survey of paramedic services in Ontario in 2013 [29] showed that six regional services were planning to provide CP programing in the future, including chronic disease management services and in-home lifestyle and safety evaluations. A systematic review of CP [6] suggested that this field is expanding quickly and there is an urgent need to establish and test models of CP programs [6, 28].

To have the greatest impact on reducing unnecessary health-care utilization, there needs to be a two-pronged approach [30]:a population-based intervention located in areas of high needan individual-focused intervention targeting specific high users identified by paramedic services

#### Population-based intervention

To address the first item, a population-based intervention, the McMaster Community Paramedicine Research Team developed the Community Health Assessment Program through Emergency Medical Services (CHAP-EMS) [31], which began as a pilot study [4], was evaluated as a 1-year randomized controlled trial (RCT) [31, 32], and is now being sustained by paramedic services under the name ‘Community Paramedicine at Clinic’ or CP@clinic. CP@clinic is a primary prevention community health promotion program that is targeted at seniors living in subsidized housing. The CP@clinic program is a free, weekly, one-on-one drop-in session held in a common area of the social housing and is open to all residents. It involves a cardiovascular disease risk assessment, blood pressure monitoring, and risk assessments for diabetes and falls. The results are sent to the participants’ family physicians. Paramedics also deliver tailored health promotion and disease prevention advice, linking residents to local community resources to assist them in changing their health behaviors and lifestyle. The RCT results for this program are showing promise in a number of different areas, including reductions in EMS calls based on participation rate, blood pressure reduction and monitoring, and improved aspects of health-related quality of life such as anxiety, depression, and mobility [32].

#### Individual-focused intervention

The research program of the McMaster CP Research Team is being expanded to a home-visit CP intervention, called CP@home, for individuals who call EMS for a lift assist or who frequently call EMS for other concerns. Briefly, the community paramedics will make home visits to those identified by the paramedic service, conduct risk assessments, refer the individual to appropriate resources to prevent future EMS utilization, and report back to their family physician. Details of this intervention and the RCT are provided in Methods/design.

The use of paramedics is ideal for this intervention as it will deal with individuals who are frail, seriously ill, or potentially unstable, and who may require immediate assistance [3]. Paramedics are an excellent fit to handle these emergent situations and also, with training, knowledgeable about health promotion and preventive medicine. Paramedics are also suited well for conducting risk assessments, since this is part of their basic training.

This home-visit intervention will complement the work already being conducted by CP@clinic and it will build on the team’s contributions to community-based care and established collaborative relationships with paramedic services, primary care, social housing, public health, and other community services. We hypothesize that the intervention will lead to a significant reduction in repeat EMS calls and ED visits from high-use individuals. This anticipated decrease in EMS calls and ED visits may have implications in terms of health-care savings and increased health-care resource capacity. It is also expected that the intervention will improve the health behaviors of participants, which may contribute to their overall health outcomes. If the study demonstrates that CP@home is beneficial in reducing the number of EMS calls and ED visits (or not), this will inform decision makers when developing CP policies and expanding the role of paramedics in other regions. Furthermore, the study data will provide the required information for an expansion of CP@home and future research studies.

### Objectives and research questions

Our primary objective is to evaluate the CP@home intervention to answer the following research questions:What is the difference in the number of repeat EMS calls from individuals who are frequent callers or who call for lift assist following CP@home, compared to their own baseline and also compared to a control group (usual care)?What is the effect of a CP intervention focused on in-home chronic disease management, community health service connection, and education on EMS usage on the rate of acute ED visits and hospital admissions in the intervention group compared to the control group?

Our secondary objectives are to examine individual health risk factors (e.g., blood pressure, anxiety, and depression) and additional health utilization outcomes (e.g., primary care visits) in this population. The intervention will also provide a baseline, cross-sectional description of the characteristics of individuals who repeatedly call EMS in Canada, which has been identified as a gap in the current literature [9]. We will also assess the cost-effectiveness of the program by conducting an economic analysis. Finally, we will assess process outcomes (e.g., number of referrals and participant satisfaction) using qualitative and quantitative methods. This report presents Version 3 (3 May 2018) of the study protocol. We followed the Standard Protocol Items Recommendations for Interventional Trials (SPIRIT) Statement 2013 (Additional file 1).

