## Methods/design

### Study design

A mixed-methods study design will be used to answer our research questions. An RCT will be conducted in which all community residents meeting the study criteria will be allocated to receive either the CP@home intervention or usual care (control). Primary and secondary outcomes will be evaluated using parallel comparisons between the intervention and control groups as well as comparisons within groups before and after the intervention is implemented (i.e., using baseline metrics). Qualitative and quantitative process evaluation will be conducted to assess for efficiency of intervention delivery, participant compliance, participant satisfaction, and ways of improving the intervention. The qualitative and quantitative process evaluation will help to generate information on experiences with the program and how to improve it. This study has been approved by the Hamilton Integrated Research Ethics Board. Any amendments will be submitted to the ethics board for approval and revisions made to the clinicaltrials.gov registry, as appropriate.

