### Sample size

Our sample size was calculated based on the mean difference in the number of ambulance calls between the intervention and control groups in 6 months. The mean number of ambulance calls per frequent user was 5.3 (standard deviation = 5.7) over a 6-month period for a local paramedic service. Using EMS reductions as our primary outcome for the sample size calculation and the *t*-test as our method of analysis, we will need 261 participants per group to detect a 25% difference between groups assuming standard parameters (alpha = 0.05 and power = 0.8). This difference is considered clinically significant, and a change in one call per high user could result in a resource savings of CAD 1626.00 per participant [4].

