### Primary and secondary outcome measures

The primary outcome measure will be the number of repeat EMS calls resulting in the dispatch of an ambulance. The secondary outcomes are the number of ED presentations, the number of hospital admissions in the study populations both 6 months before and after the intervention start date, the number of referrals to community services, and the number of referrals to family physicians. We will also obtain a cross-sectional description of the frequent EMS user population.

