### Data gathering procedures

The primary and secondary outcomes will be assessed over two time periods: the 6 months prior to the start of the intervention and the 6 months after the initiation of the intervention. Data will be collected from: (1) the local paramedic service databases (EMS call volumes), (2) the CP@home database, which is completed by the community paramedics (health risk assessments, quality of life, other health-related scales, and community referrals), and (3) administrative databases (ED visits, hospital admissions, and primary care visits). Administrative data will be collected pre- and post-intervention, as well as during the study. Table 1 summarizes the outcomes, data sources, and analyses. Data will be transferred from the paramedic services to the study team through a secure, encrypted virtual private network.

**Table 1 Tab1:** Summary of outcomes, data sources, and analysis

Outcome	Data source(s)	Data analysis
Primary		
Number of repeat EMS calls resulting in ambulance dispatch in the study population	Paramedic services administrative data	- Comparison between intervention and control groups after the 6-month intervention - Multi-level modeling of factors affecting outcome
Secondary		
Number of ED presentations in the study population	Hospital and ED database Paramedic services administrative data	- Comparison between intervention and control groups after the 6-month intervention - Multi-level modeling of factors affecting outcome
Number of hospital admissions in the study population	Hospital and ED database	
Number of referrals to community services (intervention group only)	CP@home database Paramedic services administrative data	- Descriptive analysis
Number of referrals to family physicians (intervention group only)	CP@home database Paramedic services administrative data	
Tertiary		
Characteristics of frequent users (baseline only)	CP@home database	- Descriptive analysis
Cost-effectiveness of CP@home	CP@home database Paramedic services administrative data	- Economic analysis
Process		
Number of CP@home visits	CP@home database	- Descriptive analysis - Thematic analysis
CP@home participant satisfaction	Self-administered survey Key informant and individual interviews of participants and paramedics	

*ED* emergency department, *EMS* emergency medical services

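### The primary question includes a before-after contrast distorted by selection on recent calls; only the randomised between-arm contrast should answer it

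*Protocol article*

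**What the plan says.** **Objective.** The protocol article, under Objectives and research questions, puts two questions under the primary objective. The first asks for the difference in repeat EMS calls "compared to their own baseline and also compared to a control group (usual care". The second concerns the effect "on the rate of acute ED visits and hospital admissions in the intervention group compared to the control group".

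**Design.** Study design says that primary and secondary outcomes will be evaluated by parallel comparisons between arms, "as well as comparisons within groups before and after the intervention is implemented (i.e., using baseline metrics".

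**Entry.** Participants gives three routes: three or more calls in 6 months with at least one in the previous month; a lift-assist call in the previous month; or direct referral by paramedics, with no call threshold.

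**Windows.** Data gathering procedures assesses outcomes over "the 6 months prior to the start of the intervention and the 6 months after the initiation of the intervention".

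**Where the analysis is made concrete.** Sample size is built on the difference between groups. Table 1 lists, for the primary outcome, a between-group comparison and multi-level modelling, and no before-after analysis. Data analysis specifies intention to treat.

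**Outcome labels.** Primary and secondary outcome measures names EMS calls as the primary outcome and continues: "The secondary outcomes are the number of ED presentations, the number of hospital admissions". Table 1 agrees.

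**The concern.** The entry rule and the baseline draw on largely the same months. Someone who enters on three calls in 6 months has at least three calls in a baseline that covers those months, while nothing requires any call in the 6 months afterwards. Some of these people have a persistently high rate. Others had an unusually bad half-year and will drift back toward their usual rate. The group mean is therefore expected to fall without treatment.

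The before-after contrast in the intervention arm mixes that fall with any effect of CP@home and cannot separate the two. The article does not mention regression to the mean, does not rank the two contrasts, and does not call the before-after one descriptive. Half of the stated primary question could thus receive a favourable answer from an ineffective programme. The results are meant to inform community paramedicine policy, so the misreading would have consequences.

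**Working it through.** **1. Inputs from the article.** From Sample size: "The mean number of ambulance calls per frequent user was 5.3 (standard deviation = 5.7) over a 6-month period"; and "we will need 261 participants per group to detect a 25% difference between groups". The target difference is 0.25 × 5.3 = 1.325 calls.

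**2. The article's own figure.** Two-sided alpha 0.05 is assumed, since sidedness is not stated. With power 0.80:

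n = 2 × (1.960 + 0.842)² × 5.7² / 1.325² = 2 × 7.849 × 32.49 / 1.7556 = 290.5, so 291 per group (292 with the exact t-test).

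The stated 261 is not reproduced. A difference of 1.4 calls (1.4/5.3 = 26.4%) gives 260.2, so 261. Power at 261 for 1.325 calls is about 76%. This is a separate matter: the point here does not depend on it, and 261 is used below only as the size of one arm.

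**3. Why a fall is expected.** Let each person have a stable rate λ (mean calls per 6 months), with baseline and follow-up counts independent Poisson(λ) and no treatment effect. If λ varies as a gamma distribution with shape k and mean m, then for a selected group

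expected follow-up = (k + mean baseline) × m / (k + m).

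With k = 1 and m = 2, people with three or more calls average 5.00 at baseline. Expected follow-up is (1 + 5.00) × 2/3 = 4.00, a fall of 20%. The baseline SD in this model is only 2.45, well below 5.7, so it shows the mechanism but does not fit the article's figures.

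**4. Models near both stated moments.** The distribution of λ is an assumption: log λ normal with mean μ and SD σ. Frequent user is not defined in Sample size, so taking it as the entry rule is also an assumption. Simulation with no treatment effect gives:

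| μ, σ | Selection | Baseline mean (SD) | Follow-up mean | Fall | Paired z, n = 261 |
|---|---|---|---|---|---|
| −2.5, 1.65 | ≥3 calls | 5.34 (5.41) | 4.07 | 24% | 7.3 |
| −3.5, 1.80 | ≥3 calls | 5.14 (5.27) | 3.81 | 26% | 7.9 |
| −1.5, 1.50 | ≥3 calls | 5.70 (5.84) | 4.53 | 20% | 6.4 |
| −1.0, 1.35 | ≥3 calls | 5.51 (4.96) | 4.35 | 21% | 6.5 |
| −5.5, 1.95 | ≥3 calls, ≥1 in last month | 5.28 (6.04) | 3.60 | 32% | 10.3 |

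Paired z = mean fall × √261 / SD of the individual differences. In the first row the mean fall is 5.34 − 4.07 = 1.27 calls and the SD of differences is about 2.8, so z ≈ 1.27 × 16.16 / 2.8 = 7.3. The 1.27 calls compares with the 1.325 calls that the trial is designed to detect.

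**5. Sensitivity.** Across all distributions tried, including ones far from 5.3 (SD 5.7), the fall for people with three or more calls ranges from 7% (a gamma model with baseline mean 8.53) to 50%. Even the 7% fall gives z = 2.4. Selecting only on any call in the last month, as a stand-in for the lift-assist route, gives 7 to 58%.

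**6. The randomised contrast.** Both arms are selected by the same rule and regress equally. In the first row the expected follow-up mean is 4.07 in each arm, a difference of 0. The expected difference in change is 1.27 − 1.27 = 0.

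**The case against.** The strongest reply is that the confirmatory analysis is already between-arm wherever it is made concrete: the sample size, Table 1 and the intention-to-treat statement. The design applies the before-after comparison to both groups, so the control arm's fall would appear beside the intervention arm's and expose the artefact. No within-group test, p-value or alpha is mentioned, and such detail is commonly left to an analysis plan. This stands as far as it goes, and it confines the defect to one contrast and its standing. It does not remove the defect, because the own-baseline comparison is a stated part of the primary question, not an omitted detail.

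Stronger readings are tempting but not supported:

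- A reader might infer that the trial could declare success without a between-arm difference. No success rule in the article rests on the before-after contrast.
- A reader might infer that a fall is certain. It is expected if rates are stable. The Background calls these people frail, seriously ill or potentially unstable, and rising rates could offset it.
- A reader might infer that requiring a call in the last month enlarges the fall. As a percentage it does not generally do so: with μ = −2.5 and σ = 1.65, adding it changes the fall from 24% to 21%.
- A reader might treat everyone as selected on high calling. The lift-assist route needs one call, the referral route needs none, and the mix is not given.

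The placing of question 2 is a labelling conflict only. That question compares with control alone and is free of this bias.

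**Conclusion.** The point holds for the before-after contrast and for its place in the primary question; the randomised comparison is sound. With stable rates and no effect of CP@home, calls among frequent callers would fall by roughly 20 to 30% in models close to the stated mean and SD, about the size of the target effect. The direction rests on stable individual rates. The size rests on an assumed distribution of rates and on reading frequent user as three or more calls in 6 months. What needs correcting is that a confounded contrast stands level with an unbiased one, without a statement of which answers the primary question.

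**What to change.** - **Objectives and research questions:** word the primary question as the between-arm difference in EMS calls over the 6 months after the start, and remove the own-baseline comparison from it.
- **Study design:** state that the between-arm contrast is the sole primary contrast, with each participant's 6-month baseline count as a covariate. Show before-after means for both arms side by side, descriptively, with no effect claims.
- **Question 2, separately:** list ED visits and hospital admissions under the secondary objectives, to agree with Primary and secondary outcome measures and Table 1.

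The cost is wording. The baseline counts are already to be collected, and the change brings the objectives into line with the sample size and Table 1. The investigators give up uncontrolled before-after claims of effect.

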**Fig. 1 Fig1:**
[figure not shown]
Study flow diagram

We have secured a waiver of consent for both intervention and control participants prior to randomization since all baseline data collected on participants will be from de-identified secondary data sources. Post-randomization, participants allocated to the intervention group can opt out from receiving the CP@home intervention and no identifiable information will be collected from this group. Those who agree to receive the CP@home intervention will be asked to provide consent since individual information will be collected as part of the intervention and evaluation process.

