Physical measures (such as blood pressure), risk assessment scores, and process measures will be collected during the home visits and stored in the CP@home electronic database. Participant satisfaction will be collected through a post-intervention self-administered electronic survey and key informant interviews (KIIs). All participants will be invited to answer the self-administered electronic survey. Six intervention participants and two paramedics implementing the intervention from each site will be invited to participate in the KIIs. The surveys will be conducted during the last CP@home intervention visit. The KIIs will be conducted 6 months after the initiation of the intervention. Participants recently enrolled to the intervention and paramedics who have been implementing the program for at least 1 month in the previous 3 months will be included in the KIIs to maximize the richness of the information and minimize recall bias.

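### The profile labelled as frequent users is built from consenting intervention participants on any of three entry routes, and only one route requires repeated calls

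*Protocol article*

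**What the plan says.** All references are to the protocol article.

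- **Target of the description.** Objectives and research questions promises a "cross-sectional description of the characteristics of individuals who repeatedly call EMS in Canada", to fill a gap in the literature. Primary and secondary outcome measures adds: "We will also obtain a cross-sectional description of the frequent EMS user population". Table 1 lists the tertiary outcome as "Characteristics of frequent users (baseline only", with descriptive analysis.
- **Source of the data.** Table 1 gives one source for this outcome, the CP@home database. Data gathering procedures describes it as "the CP@home database, which is completed by the community paramedics" and says that physical measures, risk scores and process measures "will be collected during the home visits and stored in the CP@home electronic database".
- **Who is in that source.** Under Allocation of intervention, "Those who agree to receive the CP@home intervention will be asked to provide consent". Those allocated to the intervention "can opt out from receiving the CP@home intervention and no identifiable information will be collected from this group". Controls receive no home visits.
- **Who can enter.** Participants requires any one of three conditions: at least three calls in 6 months with one in the previous month; a lift-assist call in the previous month; or direct referral by paramedics, with no call count or time window.
- **What counts as frequent.** The Abstract attaches the term frequent callers to the three-call route only and names the other two routes separately. The Background section on frequent EMS users gives four or more calls in a year and adds that "definitions range from three to ten times per year".

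**The concern.** The label of the outcome and the people who supply its data do not match. Two of the three routes carry no requirement of repeated calling, yet everyone visited and consented enters the same database, and that database is the sole source of a table headed frequent users. No section restricts the table to the call-count route or asks for it by route.

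The stake is the descriptive aim. The article says that no study of the characteristics of frequent EMS users in Canada was found and offers this profile to fill the gap. If the profile mixes frequent callers with people who called once for help after a fall, or who were referred for other reasons, readers will take its age, health and call figures as those of frequent users. They would also be figures for people who accepted home visits, which the label does not say.

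**Working it through.** The protocol gives no figure for this point, so there is nothing to reproduce. The check compares the entry routes with the label and then gives a bounded illustration.

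**Step 1: minimum calls by route** (Participants)

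| Route | Minimum calls stated | Guarantees the lowest cited definition (3 a year)? |
|---|---|---|
| Call count | 3 in 6 months, 1 of them in the last month | Yes |
| Lift assist | 1 in the last month | No |
| Paramedic referral | None stated | No |

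**Step 2: what entry on one route only implies.** A lift-assist-only participant has called in the last month and does not meet the call-count criterion, so has 1 or 2 calls in the last 6 months. Such a person could still reach 3 in a full year through earlier calls, but need not. A referral-only participant has no such bound. One with several calls, none in the last month, would also fail the call-count criterion.

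**Step 3: who is described.** The CP@home database is filled at home visits. Visits occur only in the intervention arm, and only for those who agree and consent. Controls and opt-outs are absent. Those present may have come in on any route.

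**Step 4: illustration for mean calls.** Inputs:
- 5.3 calls in 6 months per frequent user at a local paramedic service (Sample size), taken here as the mean for call-count entrants. That is an assumption, since the section does not say how it defined a frequent user.
- *q*, the share who entered only on another route. The protocol does not give it; 20%, 30% and 50% are assumed.
- *m*, the mean calls of those other entrants. This is also assumed. The lower value is 1. The upper value is 1 + 0.5 × 1 = 1.5, borrowing the Background's figure that about half of lift-assist callers call again within a month.

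Pooled mean = 5.3 × (1 − *q*) + *m* × *q*

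| *q* | *m* = 1 | *m* = 1.5 |
|---|---|---|
| 20% | 4.24 + 0.20 = 4.44 | 4.24 + 0.30 = 4.54 |
| 30% | 3.71 + 0.30 = 4.01 | 3.71 + 0.45 = 4.16 |
| 50% | 2.65 + 0.50 = 3.15 | 2.65 + 0.75 = 3.40 |

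The range is about 4.5 down to 3.2, against 5.3. If all the other entrants were lift-assist-only, Step 2 caps *m* at 2, which gives 4.24 + 0.40 = 4.64 at 20% and 2.65 + 1.00 = 3.65 at 50%.

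**The case against.** **The label may already be the restriction.** Table 1 speaks of the study population for EMS calls, ED presentations and admissions, but of frequent users for this outcome. The Abstract, the first research question and the closing discussion all name lift-assist callers apart from frequent callers. On that reading the table would hold call-count entrants only. This is a fair reading, but no section states it. The only source named holds visited participants from every route, and the Abstract's background also uses frequent users for the intervention's whole target group. The text does not settle the matter, and an analyst taking Table 1 at face value would pool.

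**Splitting a descriptive table is analysis-plan detail.** In general that is so. Here, however, the protocol itself fixes the label, the target population and the source, and these do not agree with its own entry criteria.

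**Lift-assist callers are not all infrequent.** This stands. The Background says that some older adults call often for lift assists, and that about half of lift-assist callers call again within a month. Many may also meet the call-count criterion. The misdescribed share is therefore unknown and could be small.

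**The problem can be repaired at analysis.** This is largely true. EMS call data for the prior 6 months are collected, and the team verifies eligibility before randomisation. It does need that information to be linked to the CP@home records, and Table 1 does not list it as a source for this outcome.

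**Conclusion.** The point holds as a mismatch between label and population in a descriptive tertiary outcome. As written, the plan allows an unknown share of people who meet none of the cited definitions to be described as frequent users, within a sample already limited to consenting intervention participants. The range of about 4.5 to 3.2 mean calls instead of 5.3 is an illustration. It rests on assumed values of *q* and *m*, and on 5.3 applying to call-count entrants.

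Four stronger conclusions might be drawn, and the documents do not support them:
- **The profile describes everyone eligible.** It does not. Its source leaves out controls and opt-outs.
- **Referred participants made no calls.** The referral route states no call count, which is a different thing.
- **Falls and age are inflated by a calculable amount, and mental illness and substance use diluted.** The 23% in the cited UK study is for frequent fallers, and a single lift assist does not make someone one, so the two cannot be averaged. Nothing is said about the characteristics of referred participants, so the overall direction is open.
- **The trial's comparison is compromised.** The randomised comparison of EMS calls, ED presentations and admissions does not use this profile and is unaffected.

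The change is worth making because it costs little and the profile is offered as filling a gap. It is not a reason to doubt the main results.

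**What to change.** 1. In Primary and secondary outcome measures and in Table 1, report the characteristics of frequent users for participants who met the call-count criterion, including those who also met another route. Show lift-assist-only and referral-only participants in separate columns.
2. When eligibility is verified (Allocation of intervention), record every criterion each person meets, not only the first, and carry this field into the CP@home record. Show the prior 6-month call count in every column, because some referral-only participants may be frequent callers under a yearly definition.
3. State beside the outcome that the profile covers intervention participants who accepted the visits and consented.

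The cost is one extra field at verification and two extra table columns. The frequent-user column will be smaller and slightly less precise. No data are lost, and the randomised analysis does not change.
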